## Abstract

**Background:**

In light of declining autopsy rates around the world, post-mortem MR imaging is a promising alternative to conventional autopsy in the investigation of infant death. A major drawback of this non-invasive autopsy approach is the fact that histopathological and microbiological examination of the tissue is not possible. The objective of this prospective study is to compare the performance of minimally invasive, virtual autopsy, including CT-guided biopsy, with conventional autopsy procedures in a paediatric population.

**Methods/Design:**

Foetuses, newborns and infants that are referred for autopsy at three different institutions associated with the University of Zurich will be eligible for recruitment. All bodies will be examined with a commercial CT and a 3 Tesla MRI scanner, masked to the results of conventional autopsy. After cross-sectional imaging, CT-guided tissue sampling will be performed by a multifunctional robotic system (Virtobot) allowing for automated post-mortem biopsies. Virtual autopsy results will be classified with regards to the likely final diagnosis and major pathological findings and compared to the results of conventional autopsy, which remains the diagnostic gold standard.

**Discussion:**

There is an urgent need for the development of alternative post-mortem examination methods, not only as a counselling tool for families and as a quality control measure for clinical diagnosis and treatment but also as an instrument to advance medical knowledge and clinical practice. This interdisciplinary study will determine whether virtual autopsy will narrow the gap in information between non-invasive and traditional autopsy procedures.

**Trial Registration:**

ClinicalTrials.gov: NCT01888380

## Background

Despite the long-standing clinical success of post-mortem examinations [1], there has been a sustained decline in autopsy rates around the world [2]. This development has been observed not only in adults, but even more frequently in neonates, infants and children [3-5]. This is in spite of the fact that perinatal and paediatric autopsies present particular value in several regards.

First, perinatal post-mortem examinations allow for the identification of genetic and obstetric factors that are of relevance to the management of future pregnancies, allowing for appropriate counselling of families. In approximately 30% of cases following termination of pregnancies, foetal autopsy changed the recurrence risk associated with those parents [6,7]. Second, foetal and paediatric autopsies are important in confirming or refuting pre-morbid diagnoses, and present information pertinent to further specific diagnoses. Stambouly et al. demonstrated that paediatric autopsies reveal additional findings in up to 50% of cases, approximately 10% of which identified diagnoses that may have prevented death had they been known [8]. Finally, in addition to the benefits to individuals and families, autopsy has the potential to advance medical knowledge and improve clinical practice [9].

The reasons for the decrease in autopsy rates are multifactorial and complex. Importantly, a large majority of parents deny consent to autopsy because of concerns about disfigurement of their deceased child during the procedure. The desire for their infant to “be left in peace” and scepticism concerning other potential benefits or detriments are additional causes for this denial [10,11]. Additionally, the controversial perception that improved technology renders the autopsy redundant may have altered the interest and attitude of the public and clinicians towards traditional post-mortem examinations.

Questions have therefore arisen regarding the merit of traditional autopsy as a means of quality control for clinical diagnosis and treatment. For this reason, many clinicians have called for a minimally invasive autopsy technique that may be better accepted by parents and healthcare professionals and could therefore provide an alternative for those parents for whom traditional autopsy is not an option. Previous studies have indicated a better acceptance of such an autopsy approach among both healthcare professionals [12] and parents [13].

Less invasive methods, such as post-mortem ultrasound- and laparoscopic examinations [14], have been reported in the last two decades. However, these methods did not gain widespread acceptance due to a lack of evidence from studies comparing such an approach with conventional autopsy in a rigorous and blinded manner. Post-mortem magnetic resonance imaging (post-mortem MRI) and computed tomography (CT), which are generically referred to as post-mortem cross-sectional imaging [15], are other non-invasive autopsy techniques first reported in 1996 [16]. The procedures have the advantage of determining the position of the different organs in situ while maintaining the integrity of the human body. Numerous studies have now investigated the diagnostic accuracy of post-mortem MRI compared to conventional autopsy. Most of them showed good results in the detection of central nervous system abnormalities, but relatively poor results for the detection of cardiac anomalies [17-21]. The most recent and so far the largest, prospective validation study in foetuses and children demonstrated an overall concordance of 89.3% regarding the cause of death or major pathological lesions detected by minimally invasive autopsy (post-mortem MRI and blood sampling) compared with conventional autopsy [22]. In children and adolescents, the concordance was generally lower than in foetuses (53.6% vs. 94.6%), mainly because of undetected sepsis affecting the lungs, the heart, and the intestine, or because of disseminated sepsis.

In such scenarios, analysis of microstructure at the electron microscopic level as well as specific staining, would be informative [23]. However, this is not possible with an imaging-based, non-invasive autopsy approach. To overcome this shortcoming, percutaneous organ biopsies with or without image guidance have been proposed [24,25]. Biopsies leave only minor lesions and enable processing of specimens in a similar manner as those obtained by conventional autopsy. Major limitations include the relatively small amount of tissue that can be collected and the risk that the best representative parts are missed. Breeze et al. investigated the feasibility of percutaneous foetal organ biopsies using ultrasound guidance ± surface landmarks in the context of a minimally invasive autopsy. They reported that this technique cannot yet be considered to provide useful clinical information, because less than 50% of all biopsies were adequate for histological examination [26]. Percutaneous needle biopsies under CT guidance are therefore suggested to be a more reliable method for targeted sampling of tissue probes, narrowing the information gap between non-invasive and traditional autopsy [27]. However, a large prospective study of such a minimally invasive autopsy approach by post-mortem cross-sectional imaging and CT-guided biopsies in foetuses, newborns and infants has not been conducted. With the proposed interdisciplinary study, we aim to compare the performance of combined cross-sectional imaging and CT-guided biopsy with conventional autopsy. For this project, an approach that combines post-mortem imaging and imaging guided biopsies is defined as minimally invasive or virtual autopsy.

## Methods/Design

### Trial design

This is a prospective, comparative, interdisciplinary, clinical trial with three study sites: the Department of Neonatology of the University Hospital Zurich, the Children’s University Hospital Zurich and the Institute of Forensic Medicine. All three study sites are associated with a single academic institution – the University of Zurich, Switzerland. Consecutive foetuses, newborns and infants that are referred for autopsy at these three institutions will be eligible for recruitment into the study. All recruited cases will undergo post-mortem imaging (MRI and CT) with CT-guided biopsies in addition to conventional autopsy.

The study protocol was submitted Ethical Committee of the Canton Zurich and received a waiver from ethics approval. Clinical trial registration was made at clinicaltrials.gov under the number NCT01888380. The study will be conducted in accordance with principles enunciated in the current version of the Declaration of Helsinki, the guidelines of Good Clinical Practice issued by the International Conference on Harmonization, and the requirements of the Swiss regulatory authority. With the exception of forensic cases, parental consent will be required for each subject.

### Inclusion and exclusion criteria

Inclusion criteria for participation in the paediatric virtual autopsy trial comprise still- and live-born infants from 16 weeks of gestational age up to 12 months postnatal age regardless of the manner of death (trauma, homicide, or intoxication). Deceased infants who are organ donors will be excluded from the study.

### Objectives

Our primary objective is to compare the accuracy of post-mortem imaging combined with guided biopsy for the detection of the cause of death and/or major pathological lesions to that of conventional autopsy in foetuses, newborns and infants. Secondary objectives primarily aim to evaluate which clinical indications are best suited to each of the two approaches. Second, we aim to optimise a protocol for MRI examinations in deceased neonates, infants and children. Third, this study aims to report the number of cases in which there is a change in the ante-mortem diagnosis following post-mortem cross-sectional imaging using CT-guided biopsy.

### Recruitment

As routinely practiced, post-mortem examinations will be offered for all foetuses, newborns and infants up to 12 months of age regardless of whether the death was due to a natural or non-natural cause. In non-medical legal cases, parents will be approached by appropriately trained staff (a consultant or an experienced midwife) and asked if they consent to an autopsy for their child. If parents agree, a precedent cross sectional imaging with CT-guided biopsy will be proposed. They will receive an information leaflet and at least one parent must give written consent.

### Post-mortem imaging

All bodies will be examined with a commercial dual-source CT (Somatom Definition; Siemens Medical Solutions, Forchheim, Germany) and a 3 Tesla MRI scanner (Philips Achieva; Philips Medical Systems, Best, The Netherlands) at the Institute of Forensic Medicine, University of Zurich. MR images will be acquired as given in Table 1 and will include the complete foetal or infant body from the calvarium through the lower extremities. The first 30 subjects will be used to improve the imaging sequences and to optimise the robotic system allowing for CT-guided tissue sampling. These subjects will not be included in the main study. Initially, a specialised forensic radiologist ([name]) with 6 years of experience in post-mortem radiology will report the results of MR and CT imaging in a large internet-based secure database (SecuTrial®). All diagnoses will be specified according to the international classification of diseases (ICD-10).

**Table 1 T1:** Sequences for post-mortem magnetic resonance imaging

**Sequence**	**Slice thickness (mm)**	**TR (ms)**	**TI (ms)**	**TE (ms)**	**IR delay (ms)**
**Body Imaging**					
T2 coronal	2	2969		100	
T2 SPIR coronal	2	3155		100	
T1 IR coronal	2	7000	600	15	600
T2 axial	2	4000		80	
T2 SPIR axial	2	3341		60	
T1 IR axial	2	7000	600	15	600
T2 sagittal	2	2969		100	
**Brain Imaging**					
T2 axial	2	5531		50	
FLAIR axial	2	12000	2850	140	2850
T1 IR axial	2	7000	600	15	600

*TR*, relaxation time, *TI*, inversion time, *TE*, echo time, *IR*, inversion recovery, *mm*, millimetre, *ms*, millisecond, *SPIR*, spectral presaturation with inversion recovery, *FLAIR*, fluid attenuated inversion recovery.

### CT-guided tissue sampling

After cross-sectional imaging, CT-guided tissue sampling will be performed by a multifunctional robotic system at the Institute of Forensic Medicine, University of Zurich. This “Virtobot System” allows for automated post-mortem biopsies and is composed of a six-axis industrial robotic arm (Stäubli TX90L; Stäubli, Freienbach, Switzerland) that has been mounted to an external axis, aligned with the CT table [28]. For performing biopsies, the Virtobot has been combined with a surgical navigation system. Under close monitoring by a forensic pathologist specialising in paediatric forensic medicine, the same predefined organs (surface of the brain including the meninges, upper and lower lobes of the lung, right and left lobe of the thymus, right and left heart ventricle, right and left lobe of the liver, both kidneys, adrenal glands, pancreas, and spleen) will be biopsied in each case. Additional samples will be taken if, based on imaging, a focal abnormality is suspected. Specimens will be fixated in formalin and examined by an independent pathologist, who is blinded to the results of post-mortem imaging and conventional autopsy results. Ancillary tests include the minimally invasive examination of the placenta and umbilical cord and CT-guided extraction of blood, urine, and cerebrospinal fluid for microbiological diagnostics (cultures).

### Virtual autopsy – final classification

Based on cross-sectional imaging, histology and ancillary test results, the findings will be reclassified with regard to the likely final diagnosis and major pathological findings. An interdisciplinary team (forensic radiologist, forensic pathologist and pathologist) blinded to the findings of the conventional autopsy will decide whether one or several pathological findings are present for each organ system. This final classification based on virtual autopsy will be reported in the same database and specified according to the ICD-10.

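### The primary outcome scores imaging, biopsy and ancillary results together, while the definition and the primary objective name imaging plus guided biopsy only

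*Protocol article*

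**What the plan says.** The protocol article describes the index test in two ways.

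**Narrow description.** The Background fixes the term for this project: "an approach that combines post-mortem imaging and imaging guided biopsies is defined as minimally invasive or virtual autopsy". Trial design lists the same two components as the procedures added to conventional autopsy. The primary objective, under Objectives, is to "compare the accuracy of post-mortem imaging combined with guided biopsy for the detection of the cause of death and/or major pathological lesions", with conventional autopsy as the comparator.

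**Wide description.** The section CT-guided tissue sampling adds a separately labelled group: "Ancillary tests include the minimally invasive examination of the placenta and umbilical cord and CT-guided extraction of blood, urine, and cerebrospinal fluid", the fluids being for culture. The section Virtual autopsy – final classification then states its inputs: "Based on cross-sectional imaging, histology and ancillary test results, the findings will be reclassified". It gives the result the same name as the narrow test: "This final classification based on virtual autopsy will be reported in the same database".

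**What is scored.** Under Sample size calculation and statistical analysis, the primary outcome is the percentage of cases in which virtual autopsy gets the diagnostic category right against conventional autopsy, with a Wilson 95% interval. With 100 cases, the stated half-widths are 8, 6 and 4 points at true values of 80%, 90% and 95%.

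**What is recorded on the way.** Under Post-mortem imaging, the forensic radiologist "will report the results of MR and CT imaging in a large internet-based secure database". Biopsy specimens are read by a pathologist who does not know the imaging or autopsy results. The next classification described is the final one, which already includes the ancillary results.

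**The concern.** One name covers two tests. The primary objective asks how accurate imaging with guided biopsy is, and the primary outcome measures imaging, biopsy and ancillary tests together. If the placenta, the cord or another ancillary result alone supplies the correct category, the case is scored as correct and will be read as a success of scanning and biopsy.

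This bears on the purpose of the trial. The Background argues that guided biopsy should narrow the information gap between non-invasive and conventional autopsy. If other sources of information enter at the same step as histology, a gain over the imaging report cannot be credited to biopsy from the classifications described. A judgement on imaging plus biopsy made after the team has seen the ancillary results would no longer be independent of them.

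**Working it through.** **1. Components named in each place (protocol article)**

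| Section | Imaging | Guided biopsy | CT-guided fluids for culture | Placenta and cord |
|---|---|---|---|---|
| Background (definition) | yes | yes | not named | not named |
| Trial design | yes | yes | not named | not named |
| Objectives (primary) | yes | yes | not named | not named |
| CT-guided tissue sampling | – | yes | yes, as ancillary | yes, as ancillary |
| Virtual autopsy – final classification | yes | yes (histology) | yes, via ancillary results | yes, via ancillary results |
| Sample size and statistical analysis | scores virtual autopsy | same | same | same |

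The placenta and cord are also absent from the list of predefined organs to be biopsied, and the MR coverage described is of the foetal or infant body.

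**2. The plan's own precision figures**

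Inputs: N = 100; p = 0.80, 0.90, 0.95; z = 1.96.

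Simple half-width = z × √(p(1 − p)/N):
- 80%: 1.96 × √(0.80 × 0.20/100) = 1.96 × 0.0400 = 7.84 points
- 90%: 1.96 × √(0.90 × 0.10/100) = 1.96 × 0.0300 = 5.88 points
- 95%: 1.96 × √(0.95 × 0.05/100) = 1.96 × 0.0218 = 4.27 points

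These round to the stated 8, 6 and 4. The Wilson half-widths are 7.77, 5.96 and 4.51. The sample size and interval widths are not affected by this point. What is in question is which test the percentage describes.

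**3. How far the two percentages could differ**

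Let X be the number of cases correct under the all-in classification, and k the number of those that are correct only because of an ancillary result. Assume that ancillary results never turn a correct answer into a wrong one. Then

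imaging-plus-biopsy percentage = (X − k)/N.

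With N = 100, each such case is worth 1 point. The documents give no value for k, so the values below are assumptions that show the range (Wilson 95% intervals in brackets).

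| k | If all-in is 80/100 | If all-in is 90/100 |
|---|---|---|
| 0 | 80% (71.1–86.7) | 90% (82.6–94.5) |
| 5 | 75% (65.7–82.5) | 85% (76.7–90.7) |
| 8 | 72% (62.5–79.9) | 82% (73.3–88.3) |
| 10 | 70% (60.4–78.1) | 80% (71.1–86.7) |
| 20 | 60% (50.2–69.1) | 70% (60.4–78.1) |

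At k = 0 nothing changes. At k = 8 the gap equals the 8-point half-width that the plan accepts at 80%.

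**The case against.** The strongest reply is that the wide test is declared openly. The final-classification section lists all its inputs and calls the result virtual autopsy, and the statistical section scores that. The Abstract speaks of virtual autopsy as including CT-guided biopsy, which leaves room for other parts. Assessing the whole minimally invasive pathway is a legitimate design. This stands so far as the percentage is valid for the composite. It does not remove the conflict with the express definition in the Background or with the primary objective.

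Several stronger readings are tempting, and the objection defeats them:

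- **That cultures lie outside the test.** The fluids are taken by CT-guided extraction and described under CT-guided tissue sampling. The Abstract and the Discussion both give missing microbiology as a drawback of imaging-based autopsy. Cultures can fairly be counted as image-guided sampling.
- **That a shared placenta forces the two methods to agree.** The section on conventional autopsy does not mention the placenta. Even if both methods use it, two independent, blinded teams can disagree.
- **That any inflation is concentrated in stillbirths.** No case mix is given, and eligibility runs to 12 months after birth.
- **That imaging-plus-biopsy accuracy could never be recovered.** Imaging and histology are read separately, and nothing says the component results are discarded. What is missing is a described team classification made before the ancillary results are known.

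**Conclusion.** The point holds as an inconsistent definition of the index test. Background, Trial design and Objectives name imaging plus guided biopsy, while the classification scored for the primary outcome also draws on ancillary results. Placenta and cord examination is the clear addition, and the status of the cultures is open to either reading.

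The effect is 1 percentage point per 100 cases for each case that only an ancillary result answers. The number of such cases is unknown and may be zero. A reader might infer an established upward bias, for example 5 to 10 points if imaging plus biopsy were right in 80 of 100 cases and ancillary results supplied a quarter to a half of the other 20 (0.25 × 20 = 5; 0.5 × 20 = 10). The documents do not support that. The fraction has no source, 80% is only a planning scenario, and the result restates the assumption.

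Nor do the documents show that the composite is the wrong primary measure. Which classification should be primary is the sponsor's choice, but it must be stated and must match the objective.

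**What to change.** 1. Have the same blinded interdisciplinary team enter and lock an ICD-10 classification from imaging plus guided-biopsy histology before the placenta, cord and other ancillary results are opened. State whether the CT-guided fluid cultures belong to this first entry.
2. Have the team then open the remaining results and enter the all-in classification.
3. Report both percentages against conventional autopsy with Wilson 95% intervals, and the number of cases whose scoring changed between the two entries.
4. State which percentage is primary, and bring the definition in the Background, the Trial design, the primary objective, the final-classification section and the statistical section into agreement. If the all-in classification is primary, the definition and the objective should name the ancillary tests.

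The cost is one extra entry per case at the same team review and one extra percentage in the report. No further staff, samples or tests are needed. The imaging-plus-biopsy figure may come out lower than the all-in figure. The lock has to be in place before main-study cases are classified.

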### Conventional autopsy

All conventional autopsies, the gold standard against which the virtual autopsy is assessed, will be performed by experienced perinatal, paediatric and forensic pathologists according to the guidelines of the Swiss Society of Pathology [29]. A database with independent access portals will be used to maintain blinding from virtual autopsy results. For each organ system, the same categorisation (likely final diagnosis and major pathological findings) will be used and specified according to the ICD-10.

### Sample size calculation and statistical analysis

A sample size of 100 cases allows for the computation of a 95% confidence interval of width +/− 8% for the primary outcome if the true percentage of cases for which virtual autopsy correctly identifies the diagnostic category is 80%. The width of the confidence interval will decrease to +/− 6% if the true percentage is 90%, and further decrease to +/− 4% if the true percentage is 95%. This precision is considered as sufficient to determine the quality of virtual autopsy.

The diagnoses established by the two methods and by the two independent teams will be compared, with the autopsy results considered the gold standard. The primary outcome will be the percentage of cases for which virtual autopsy correctly identifies the diagnostic category, which will be given together with a 95% confidence interval. Sensitivity, specificity and predictive values will be calculated for each diagnostic category, as referenced to the gold standard, again with a 95% confidence interval. Because of the small sample sizes, the confidence interval by Wilson will be used throughout, as recommended in Altman et al. in Chapters 6 and 10 [30]. Finally, the results of the virtual autopsy will be assessed with regard to the accuracy of associated lesions, the clinical utility of the information and the determination of the cause of death.

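### The abstract says the study will determine whether virtual autopsy narrows the information gap, but no planned analysis scores imaging alone, so this further stated aim cannot be answered as written

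*Protocol article*

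**What the plan says.** The Discussion paragraph of the abstract states: "This interdisciplinary study will determine whether virtual autopsy will narrow the gap in information between non-invasive and traditional autopsy procedures". The Background fixes the terms: "an approach that combines post-mortem imaging and imaging guided biopsies is defined as minimally invasive or virtual autopsy", while the imaging-based approach without tissue is called non-invasive. The Background also gives the reason for adding CT-guided biopsy, namely "narrowing the information gap between non-invasive and traditional autopsy".

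Under Objectives, the primary aim reads "compare the accuracy of post-mortem imaging combined with guided biopsy for the detection of the cause of death and/or major pathological lesions", set against conventional autopsy. The first secondary aim is to "evaluate which clinical indications are best suited to each of the two approaches". The others concern the MRI protocol and changes from the ante-mortem diagnosis after the combined procedure.

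Under Sample size calculation and statistical analysis: "The diagnoses established by the two methods and by the two independent teams will be compared, with the autopsy results considered the gold standard". As primary outcome, the plan takes the percentage of cases in which virtual autopsy finds the right diagnostic category. Sensitivity, specificity and predictive values use the same reference.

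Two recording steps precede this. Under Post-mortem imaging, a forensic radiologist initially "will report the results of MR and CT imaging in a large internet-based secure database", with ICD-10 diagnoses. Under Virtual autopsy – final classification, a three-person team then works from imaging, histology and ancillary tests, and "the findings will be reclassified with regard to the likely final diagnosis and major pathological findings", in the same database and coding.

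**The concern.** To say that a gap has narrowed, one needs its size before and after. Here that means agreement with autopsy for imaging alone and agreement for imaging plus biopsy. The plan estimates only the second. A high combined percentage could arise because biopsy helped, or because imaging was already good in these cases. The planned output cannot tell these apart.

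Without an internal comparator, a reader will turn to the 89.3% concordance cited in the Background. That figure comes from another cohort and from MRI plus blood sampling, so it is not an imaging-only figure. It also depends heavily on case mix: the same study is reported as 94.6% in foetuses and 53.6% in children and adolescents, whereas this trial stops at 12 months. A conclusion about narrowing that rests on it would not be supported by the trial's own data.

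**Working it through.** **1. The plan's own figure.** n = 100, 95% confidence. The Wald half-width is 1.96 × √(p(1−p)/n):
- p = 0.80: 7.8 points
- p = 0.90: 5.9 points
- p = 0.95: 4.3 points

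The Wilson half-widths are 7.8, 6.0 and 4.5 points. The stated ±8, ±6 and ±4 reproduce to rounding (Wilson at 95% is 4.51, on the border). These figures describe one percentage, for the combined procedure. They carry no information on the gain over imaging alone.

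**2. Stated question against planned analyses.**

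| Place | What is compared |
|---|---|
| Abstract, Discussion | Virtual autopsy as a step between non-invasive and traditional autopsy |
| Objectives, primary | Combined procedure against conventional autopsy |
| Objectives, first secondary | Indications suited to each of the two approaches |
| Objectives, third secondary | Ante-mortem diagnosis against result after the combined procedure |
| Statistical analysis | Two methods, with autopsy as reference |

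No objective or analysis row scores imaging alone.

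**3. The external figure.** Wilson 95% limits are 88.8% to 97.8% for 95 of 100 correct and 82.6% to 94.5% for 90 of 100. Both contain 89.3%. At 99 of 100 the lower limit is about 94.6%, which excludes it. The obstacle to using 89.3% is therefore mainly the different cohort and procedure, not precision alone.

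**4. What a paired analysis in the same 100 cases would give.** Let b be the cases correct only after reclassification and c those correct only on imaging. The difference is d = (b − c)/n, with SE = √(b + c − (b − c)²/n)/n. The exact McNemar p-value comes from Binomial(b + c, 0.5). The document gives no discordance rates, so b and c are assumptions.
- b = 7, c = 1: d = 6 points; SE = √(8 − 0.36)/100 = 0.0276; CI 0.6 to 11.4; p = 2 × (1 + 8)/256 = 0.07.
- b = 12, c = 2: d = 10 points; SE = √(14 − 1)/100 = 0.0361; CI 2.9 to 17.1; p = 2 × (1 + 14 + 91)/16384 = 0.013.

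Exact McNemar power at the two-sided 5% level, for assumed true rates:

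| Gained / lost | Difference | CI half-width | Power |
|---|---|---|---|
| 5% / 1% | 4 points | 4.7 | 0.20 |
| 10% / 2% | 8 points | 6.6 | 0.56 |
| 15% / 5% | 10 points | 8.5 | 0.54 |
| 15% / 2% | 13 points | 7.7 | 0.90 |
| 20% / 5% | 15 points | 9.4 | 0.84 |

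Twelve corrected cases require at least 12 imaging errors, so imaging-only accuracy of at most 88%.

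**5. What that difference contains.** Between the two readings, histology is added. So are ancillary tests: cultures of blood, urine and cerebrospinal fluid, and examination of placenta and cord. The reader also changes, from one radiologist to a team of three. The difference is the sum of all of these.

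**The case against.** The strongest reply is that the primary objective concerns the combined procedure against conventional autopsy, and the primary analysis estimates exactly that. This stands. A reader might infer that the trial misses its main question or that its primary result is invalid. The document does not support that. The mismatch is with the abstract's closing claim and the rationale in the Background.

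A second reply is that this is a condensed article and a staged secondary analysis may exist in a fuller plan. The separate imaging entry and the later reclassification are compatible with that, but do not show it. The article does state its objectives, primary outcome and comparison, and none contains the contrast that its claim needs.

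A third reply is that a paired difference would not isolate biopsy, and that it may be inconclusive. Both parts stand. In infection, for instance, cultures could drive the gain. It is also tempting to call the within-case comparison much sharper than the one with 89.3%. That would set an assumed gain of about 10 points against a gap of 95 − 89.3 = 5.7 points. At a similar size, 7 corrected against 1 spoiled, the paired p-value is 0.07. The case for pairing rests on the same cases and the same reference standard, not on a large advantage in precision.

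**Conclusion.** The point holds in limited form. The primary objective is served and nothing already planned becomes invalid. The abstract's further aim cannot be answered by the analysis as written, because imaging alone is never scored. Adding the comparison would be a cheap improvement.

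Under the assumed rates tabulated above, 100 cases give a 95% half-width of about 5 to 9 points for the gain. Gains of 13 to 15 points would probably be shown (power 0.84 to 0.90), gains of 8 to 10 points about half the time for the splits shown, and gains near 4 points seldom. This rests on the assumed discordant rates and on the radiologist's entry being usable in the final outcome categories, which the article does not say. A reader might infer that any gain found could be credited to biopsy. The described sequence does not allow that, since ancillary tests and team review enter at the same step.

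**What to change.** 1. Have the radiologist's initial entry use the same outcome categories as the final classification (likely final diagnosis and major findings for each organ system). Time-stamp and lock it before histology and ancillary results are opened.
2. Add a secondary analysis in the same 100 main-study cases: percentage correct for imaging only, percentage correct for the full virtual autopsy, and their paired difference with a 95% CI for paired proportions and the two discordant counts.
3. Label the difference as the gain from biopsy, ancillary tests and team review together. Attribute it to biopsy only if the reclassification is staged so that histology enters separately, with the reader held constant.
4. Base any conclusion that the gap narrows on this within-case difference, not on the external 89.3%. If the analysis is not added, restrict the abstract's sentence to the accuracy of the combined procedure against autopsy. If a fuller plan already contains the analysis, state it in the objectives.

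Cost: protocol wording, somewhat more recording by the radiologist, a database lock and one further analysis. No extra cases or procedures are needed. Staging would add a further classification step. The price in interpretation is limited precision for small gains, which the report should acknowledge.
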